## Abstract

**Background:**

Many brain-injured patients referred for outpatient rehabilitation have executive deficits, notably difficulties with planning, problem-solving and goal directed behaviour. Goal Management Training (GMT) has proven to be an efficacious cognitive treatment for these problems. GMT entails learning and applying an algorithm, in which daily tasks are subdivided into multiple steps. Main aim of the present study is to examine whether using an errorless learning approach (preventing the occurrence of errors during the acquisition phase of learning) contributes to the efficacy of Goal Management Training in the performance of complex daily tasks.

**Methods/Design:**

The study is a double blind randomized controlled trial, in which the efficacy of Goal Management Training with an errorless learning approach will be compared with conventional Goal Management Training, based on trial and error learning. In both conditions 32 patients with acquired brain injury of mixed etiology will be examined. Main outcome measure will be the performance on two individually chosen everyday-tasks before and after treatment, using a standardized observation scale and goal attainment scaling.

**Discussion:**

This is the first study that introduces errorless learning in Goal Management Training. It is expected that the GMT-errorless learning approach will improve the execution of complex daily tasks in brain-injured patients with executive deficits. The study can contribute to a better treatment of executive deficits in cognitive rehabilitation.

**Trial registration:**

(Dutch Trial Register):
http://NTR3567

## Background

Brain-injured patients referred for outpatient rehabilitation frequently experience difficulties with planning, problem solving, reasoning and goal directed behaviour
[1-3]. These difficulties can be characterized as executive deficits
[1,4-6] and compromise daily functioning and even functional independence
[7,8]. More specifically, dysfunction of these higher-level control processes leads to real-life everyday disorganization
[9] and even subtle executive deficits often provoke difficulties in the performance of everyday-life tasks
[10]. Because of the high prevalence of executive dysfunction in the brain-injured population
[11] and its considerable impact on everyday life, effective treatment is warranted.

### Goal management training

Based on Duncan’s
[12] theory of goal neglect, Robertson
[13] developed Goal Management Training (GMT). GMT is a rehabilitation technique aimed at helping patients with executive impairments to better structure (instrumental) activities of daily living ((i)ADL). GMT entails learning and applying an algorithm, in which complex tasks are subdivided into multiple task steps. Both, the final goal and the task steps leading to this goal have to be kept active in working memory. Unfortunately, working memory processes are often impaired in patients with executive deficits. Monitoring goal-directed behaviour and the correct execution of task steps are the main aims of GMT. GMT can be applied to (re)learn all sorts of (i)ADL tasks, for example cleaning up the living room, processing and organizing mail or making a day schedule. In Figure 
1 both the GMT algorithm and an example of its application are illustrated. Previous studies have established the efficacy of GMT
[7,11,14-17] and the training is widely applied in the field of cognitive rehabilitation. The acquisition of the algorithm and the performance of the task steps, however, relies on self-control, which is impaired in patients with executive problems
[6,18]. Consequently, errors that occur during the acquisition of the algorithm and the learning of the task steps are not corrected and may interfere with the correct acquisition of the GMT process and the correct performance of the task
[19]. Preventing the occurrence of errors during learning, also known as errorless learning, may enhance treatment effects.

**Figure 1 F1:**
[figure not shown]
**Flowchart of the GMT algorithm and an example of its application adapted from [**[20]**].**

### Errorless learning in goal management training

In errorless learning, the occurrence of errors during the learning phase is prevented in contrast to standard learning, or trial and error learning, in which errors may occur naturally. Fillingham et al.
[20] described the mechanism of errorless learning using the Hebbian learning model
[21]. Learning is described as a strenghtening of the connection between neurons that fire together. If a stimulus is followed by a reponse, the subsequent pattern of neural activitivity will be more likely to be activated again in similar situations. This means that the same response can be expected, even if it is an incorrect action
[22]. If an errorless learning approach is applied in this process, the activation of incorrect neural patterns will be prevented and erroneous actions will not be evoked.

In clinical practice, several errorless learning techniques can be applied during training of complex daily tasks. Task steps can be taught using cue cards, (feed-forward) verbal instructions and visual demonstration or modeling by the trainer
[23-25]. Several studies have shown that the quality of task performance after errorless learning is superior compared to errorful learning in patients with cognitive impairments of different aetiologies
[26-32]. Most studies on errorless learning have focussed on patients with memory deficits. In these studies the efficacy of errorless learning is explained by the mechanism that errors are not consciously corrected because of impairments in explicit memory, but implicitly consolidated through a relatively intact implicit memory system
[33-35]. However, other studies do not agree with this hypothesis and describe the benefits of errorless learning by residual explicit memory processes
[36,37]. Another mechanism that may explain the advantage of errorless learning in patients with executive disorders is that errors are not detected due to a failing error-monitoring system
[38,39] and the inability to adjust behaviour on the basis of feedback
[26]. By preventing the occurrence of errors in learning the execution of a task, both these systems are circumvented.

The main aim of the current study is to examine the efficacy of Goal Management Training using an errorless learning approach in the treatment of executive impairments in patients with acquired brain injury, focusing on (instrumental) activities of daily living ((i)ADL). Both GMT and errorless learning are two well investigated instructional methods of proven effectiveness. However, to date they have never been combined. Using an errorless learning approach in GMT may optimize both the acquisition of the GMT algorithm and the execution of complex tasks in daily living. To examine the efficacy of these combined techniques, (i)ADL task performance will be evaluated using a standardized observation scale taking correct, ineffective and missing steps into account
[27]. The primary hypothesis is that combining errorless learning and GMT will result in a more efficacious intervention, when applied to (re)learning daily tasks in patients with executive disorders after acquired brain injury. This study may contribute to a better treatment of disorganized behaviour after brain injury and improve the cognitive rehabilitation of patients with executive disorders. From a patient perspective, it might consistently contribute to enhance the functional independence of brain-injured patients.

## Methods/Design

To evaluate the efficacy of GMT in which errorless learning is integrated, this approach will be compared with conventional GMT treatment in which an errorful approach is used. This comparison will be investigated in a double blind randomized controlled trial that is registered at the Dutch Trial Register (No. NTR3567). The Medical Review Ethics Committee region Arnhem-Nijmegen approved the study (No. NL38019.091.11).

### Participants and setting

The study population consists of brain-damaged patients referred for outpatient cognitive rehabilitation. Participants eligible for the study must have executive disorders due to acquired brain injury (ABI) of non-progressive nature (i.e. traumatic brain injury, stroke) in the chronic phase of the illness. Executive deficits will be assessed by an extensive neuropsychological examination.

#### Inclusion criteria

1. Non-progressive acquired brain injury;

2. Minimal post-onset time of 3 months;

3. Being in outpatient rehabilitation;

4. Having executive deficits, as established by neuropsychological examination;

5. Living independently at home;

6. Age: 18–70 years at onset.

#### Exclusion criteria

1. Inability to speak/understand the Dutch language;

2. Severe premorbid psychiatric problems;

3. Neurodegenerative disorders;

4. Substance abuse;

5. Severe cognitive comorbidity.

#### Setting

Patients will be recruited from the Rehabilitation Medical Centre Groot Klimmendaal in Arnhem, the Netherlands and the outpatient rehabilitation clinic for brain injured patients and the department of Neurorehabilitation of the Sint Maartenskliniek in Nijmegen, the Netherlands. In the course of 18 months 64 participants will be recruited.

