### Sample size

Determination of the sample size for this study is based on data from a RCT examining the effects of a structured 6-week Goal Management Training
[17]. In each group 32 participants are required to detect an effect size of *d =* .6 with a power = .80 and α. = 05. These estimated sample sizes are comparable with other studies evaluating the efficacy of different types of GMT
[17,54].

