### Randomization and blinding

Allocation of participants to either condition will be established using a computer generated block randomization procedure (block size n = 4) without stratification. The written information to inform patients about the study only mentions that two types of GMT will be compared. To achieve participant blinding, no information will be given about specific differences between the two conditions. Assessor blinding will be achieved by filming the (i)ADL task performance of the participants. All hints of treatment condition will be avoided and performance will be scored by research assistants who are not involved in delivering GMT.

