### Statistical analysis

All data will be analyzed with IBM SPSS 19. The normality of all variables will be checked and corrected for, if necessary. The performance on the neuropsychological tests will be compared with normative data and corrected for age and education. Descriptive statistics of relevant variables will be obtained and compared for the two treatment arms using analysis of variance.

To evaluate the efficacy of GMT-errorless learning compared to conventional GMT with trial and error learning, pre- and post training data will be analyzed using a 2 × 2 repeated measure analysis of variance (General Linear Model) with treatment condition (GMT-errorless learning and conventional GMT) as between-subject factor and measurement (pre- and post-treatment) as within-subject factor. The dependent variable will be the standardized scale score (quantitative). The same analysis will be done for the secondary outcome measure, the GAS scores. Appropriate post-hoc tests will be performed and effect sizes (partial eta-squared) will be computed. Moreover, correlations will be computed between moderator variables (questionnaires and neuropsychological tests) and treatment effects (difference score: post treatment minus baseline).

The background variables of the participants in both treatment conditions are expected to be comparable (age, education level, estimation IQ) because of the randomization procedure. In case of significant differences, appropriate statistical adjustment for confounding variables will be performed (ANCOVA). All statistical tests will be two-tailed, alpha set at 0.05.

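### Recruitment of 64 equals the 2 × 32 that the sample-size statement requires, so the stated power of .80 holds only if no randomised patient is lost before the post-treatment film

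*Protocol article*

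**What the plan says.** Three places in the protocol article give the size of the trial.

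- Sample size: "In each group 32 participants are required to detect an effect size of" d = .6, "with a power = .80 and α. = 05".
- Setting: "In the course of 18 months 64 participants will be recruited".
- Abstract, Methods/Design: "In both conditions 32 patients with acquired brain injury of mixed etiology will be examined".

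The Statistical analysis section fixes the method: "pre- and post training data will be analyzed using a 2 × 2 repeated measure analysis of variance", fitted as a General Linear Model in SPSS, with "All statistical tests will be two-tailed, alpha set at 0.05".

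The order of events comes from Procedure, Interventions, Baseline and Post-treatment. Random assignment follows eligibility and consent, and is described before the sessions. Two tasks are chosen in session 2, and the baseline film follows that session. Sessions 3 to 8 come next, and the second film is made after treatment.

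**The concern.** A power calculation returns the number of patients who enter the test. Here the test compares change from the first film to the second, so a patient without both films does not contribute in the usual fit. The number recruited equals the number required, which leaves no reserve for a patient who cannot settle on two suitable tasks, stops attending or is not filmed again.

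The article makes only one power statement. If some patients are lost, that statement no longer describes the trial, and a null result would be read against a precision the trial did not have.

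**Working it through.** **Inputs.** From the article: 32 per group, d = .6, power .80, alpha .05 two-sided, 64 recruited. Allocation is taken as 1:1 from the equal groups and the "computer generated block randomization procedure (block size n = 4) without stratification" (64 / 4 = 16 full blocks). Assumed here, because the article gives no rate: loss L of 5%, 10% or 20%, equal in both arms.

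**Step 1. Recruited against required.** 2 × 32 = 64, so the margin is 64 − 64 = 0. If each patient independently had a 5% chance of being lost, the chance that none of the 64 is lost would be 0.95^64 ≈ 0.04.

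**Step 2. Reproducing the plan's 32.** For a plain two-group comparison, n per group = 2 × ((1.960 + 0.842) / 0.6)² = 43.6, so 44, or 45 with the t distribution. One-sided it is 35 or 36. The stated 32 is not reproduced. It is reached only with a pre-post correlation ρ that the article does not give:

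- ANCOVA: 43.6 × (1 − ρ²) = 32 gives ρ ≈ .52.
- Change score: 43.6 × 2(1 − ρ) = 32 gives ρ ≈ .63.

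Neither route shows a hidden allowance for loss. Because the basis of 32 is unclear, the cost of loss is worked out under two readings.

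**Step 3. Patients per arm with both films.** 32 × (1 − L) = 30.4, 28.8 and 25.6.

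**Step 4. Reading A: grant that 32 per group gives exactly 80%.** In the normal approximation, power = Φ(2.802 × √(1 − L) − 1.960). For L = 10% this is Φ(2.658 − 1.960) = Φ(0.698) = .757. The t-based values are in the table. The difference detectable with 80% power grows by 1/√(1 − L), so .6 becomes .6 / √0.90 = .63 or .6 / √0.80 = .67.

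**Step 5. Reading B: plain two-sided t-test at d = .6, noncentral t.**

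| Assumed loss | Both films, per arm | Power, reading A | Power, reading B |
|---|---|---|---|
| 0% | 32 | 80% | 66% |
| 5% | 30.4 | 78% | 63% |
| 10% | 28.8 | 76% | 61% |
| 20% | 25.6 | 70% | 56% |

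Under reading B the difference detectable with 80% power is d = .71 at 32 per arm, .75 at 29 and .79 at 26.

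**Step 6. The part due to loss.** From unrounded values, 10% loss costs .800 − .756 = .044 (A) or .656 − .609 = .047 (B). A 20% loss costs .800 − .704 = .096 (A) or .656 − .558 = .098 (B). The readings agree: 4 to 5 points at 10% and about 10 points at 20%. The step from 80% to 66% occurs at zero loss and is not part of this.

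**Step 7. What a likelihood-based model recovers.** With two time points, a patient with only a baseline film restores a fraction (1 − ρ)/2 of the variance lost for the change contrast: 25% at ρ = .5 and 18% at ρ = .64. Under reading A with ρ ≈ .63, if every lost patient had a baseline film, the variance factor at 20% loss would be 1.25 − 0.183 × 0.25 = 1.204. Power would be Φ(2.802 / √1.204 − 1.960) ≈ .72, against .71 for complete pairs in the same approximation. A patient lost before the first film restores nothing.

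**The case against.** The strongest objection is that this is an omission and not an error. The three statements of size agree with one another, and a journal article may leave an allowance for loss, replacement of patients and missing-data handling to the full protocol. The study flowchart is not visible here either. This stands in part: the absence of a paragraph on loss is no finding. What remains is that the article itself fixes a required number, an equal recruited number and a complete-pair analysis, and attaches a power of .80 to them. A fuller document could supply a loss rate, but 64 recruited would still yield 64 analysed only with replacement or analysis of incomplete cases, and the article describes neither.

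The loss rates are also assumed. Eight sessions at two a week take about four weeks, with no later follow-up, so loss may be small. At 5% the cost is about 2 points.

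Three stronger readings might be inferred, and the article does not support them:

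- **That the plan promises 32 evaluable patients per group.** It speaks of patients required, examined and recruited, and never of evaluable ones.
- **That loss takes power from 80% to 56–61%.** Most of that gap is the separate problem that 32 does not follow from the stated inputs under a plain two-group test. The planned analysis also depends on a correlation that is not given, so reading B is not the only one.
- **That only loss between the two films matters.** Randomisation is described before session 1, so patients can also be lost before the first film.

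**Conclusion.** The point holds in limited form. The stated power of .80 is tied to 32 per group, recruitment stops at exactly that number, and the named analysis uses complete pairs. The figure is therefore right, at best, for a trial that loses nobody from randomisation to the post-treatment film. Loss alone costs about 2 points of power at 5%, 4 to 5 at 10% and about 10 at 20%, under either reading of the sample size. This rests on three assumptions: the loss rates themselves, equal loss in the two arms, and the usual complete-case fit of a repeated-measures General Linear Model. It is a moderate problem that should be corrected. It does not show that the trial will lose many patients, and it does not explain why 32 falls short of 45.

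**What to change.** 1. In Setting and Sample size, state 64 as the number randomised. Add an assumed loss rate with its source, and the resulting number with both films (for example, about 29 per arm at 10%).
2. Restate the power or the detectable difference for that number, and name the formula and any pre-post correlation used. At 29 per arm a plain t-test detects d = .75 with 80% power. If 32 is justified by a stated correlation, 10% loss gives about 76% power at d = .6.
3. Replace the complete-pair ANOVA with a likelihood-based model of the two time points, including every randomised patient with at least one film. Say plainly that this limits bias if data are missing at random but restores little power, and nothing for patients lost before the first film.

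The cost is a less favourable stated figure and slightly more analysis work, with no extra patients. Raising recruitment instead to keep 32 per group with both films would take 36 per group (72) at 10% loss or 40 (80) at 20%. That alone would not give 80% power under the plain t-test, so the separate sample-size question has to be settled first.

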### Procedure

A flowchart of the study design is presented in Figure 
2. An extensive neuropsychological assessment will be performed as part of the selection procedure. Participants are eligible for the study if they have executive impairments, objectified by neuropsychological examination. As executive functioning is a multifarious concept, the neuropsychological assessment is designed to cover five of its main aspects. To assess response generation
[2] the Category Fluency test (CFT) and the Letter Fluency test (LFT) will be administered. Planning will be measured with an altered version of the Modified Six Elements Test and the Zoo Map test (subtest of BADS)
[40]. The Go/No-go task from the computerized TAP 2.1
[41] will be used to examine response inhibition. Working memory will be assessed with Letter-Number Sequencing (LNS; subtest of the WAIS III)
[42] and task switching with the Brixton Spatial Anticipation test
[43]. Specifically, the criteria for having executive disorders and to be included in the study are either a standard score of 1.5 standard deviation (SD) below the normative mean on at least two of the seven executive tests or a standard score between 1 and 1.5 SD below the normative mean on at least four of those seven tests. Moreover, to obtain a complete cognitive profile of the participants, the Rivermead Behavioural Memory Test-Third Edition (RBMT III)
[44] will be administered to assess episodic memory and the alertness subtest of the TAP 2.1
[41] will be used as a measure for attention and concentration. The National Adult Reading Test (Dutch version) (NART) will be given to estimate premorbid IQ. All neuropsychological tests will be administered by a neuropsychologist or a trained assistant.

**Figure 2 F2:**
[figure not shown]
Flowchart of the study design.

After fulfilling the inclusion criteria and obtaining the signed informed consents, participants will be randomly assigned to GMT with an errorless learning approach (experimental treatment) or to conventional GMT (treatment as usual) using trial and error learning.

### Interventions

Both treatment arms will comprise eight one-hour individual sessions, administered twice a week by trained therapists. An overview of the content of the training sessions is shown in Table 
1. Sessions 1–4 will take place at the participating centers. Sessions 5–8 will take place at the participants’ home or in the work environment, depending on the treatment goals. The first two sessions of GMT will be identical for both conditions. In the first session participants will be informed about GMT in general and about cognitive dysfunction, more specifically about executive dysfunction after acquired brain injury. In the second session each participant will choose two individual treatment goals. These treatment goals must be (i)ADL tasks and the participant has to experience difficulties performing the chosen tasks. Learning the correct execution of these (i)ADL tasks will be the main aim during the rest of the training sessions. Acceptable treatment goals are those which can be subdivided into multiple steps and should be defined in accordance with the SMART method (Specific, Measurable, Attainable, Reasonable, Timely)
[45]. After the second session a baseline assessment will take place. The execution of both treatment goals will be filmed, so that it can be evaluated later by assessors who are blind for allocation. After the baseline assessment participants will undergo training sessions 3–8 in the errorless learning condition or in the trial and error condition.

**Table 1 T1:** Content of GMT sessions for both treatment arms

**Session**	**Contents**	
1	Providing information about training;	
	Providing information about cognitive functioning after acquired brain injury in general with an emphasis on executive impairments;	
	Increasing awareness of individual executive dysfunction;	
	Preparing the setting of two individual treatment goals	
2	Setting two individual chosen treatment goals (i)ADL tasks);	
	Filling out the Goal Attainment Scale forms for each treatment goal	
	**GMT-errorless learning**	**Conventional GMT-treatment**
3	Defining steps concerning treatment goal 1 using cue cards and other errorless learning techniques	General information about GMT and the GMT algorithm
4	Defining steps concerning treatment goal 2 using cue cards and other errorless learning techniques	Filling out GMT scheme by participant concerning treatment goal 1
5	Performance of the steps concerning treatment goal 1 using errorless learning techniques	Filling out GMT scheme by participant concerning treatment goal 2
6	Performance of the steps concerning treatment goal 2 using errorless learning techniques	Performance of treatment goal 1 according to the GMT algorithm
7	Integrating the steps of treatment goal 1 into the GMT algorithm using errorless learning techniques;	Performance of treatment goal 2 according to the GMT algorithm
	Performance of treatment goal 1 according to the GMT algorithm using errorless learning techniques	
8	Integrating the steps of treatment goal 2 into the GMT algorithm using errorless learning techniques;	Improvement of GMT schemes concerning one or both of the treatment goals and/or practicing performance of one or both of the treatment goals
	Performance of treatment goal 2 according to the GMT algorithm using errorless learning techniques	

Note. Sessions 1 and 2 are the same for both conditions.

